## Introduction

Hospital admission is not without risks. Admitted patients are subject to a myriad of clinical complications that can represent important health problems, leading to an increase in morbidity and mortality. These complications are also associated with increased costs, caused not only by the increase in hospitalization time but also by the need for additional procedures and treatments, in addition to the greater absence of the patient from his usual activity. Thus, it becomes important to understand the frequency and contribution of clinical complications in hospitalized patients.

Among the most frequent complications, the occurrence of nosocomial infection stands out. In developing countries, nosocomial infections are extremely frequent, reaching more than 15 in every 100 hospitalized patients [1]. In some more severe situations, the infectious condition generates dysfunction of one or more organs, a situation called sepsis and which has high morbidity and mortality [2]. Despite its frequency, the attributable mortality of sepsis, that is, the increase in mortality that results from the occurrence of nosocomial sepsis in a patient, is unknown.

We have a lot of information on the prevalence and incidence of sepsis, and lethality in patients with sepsis, including good data from Brazil [3]. We also have some data on mortality attributable to sepsis among patients with sepsis, that is, of the total number of deaths that can be directly attribute to sepsis rather than other concomitant problems. For example, in patients

admitted to the ICU, the mortality fraction attributable to sepsis is approximately 15% in developed countries [4]. However, from the point of view of health management, it is essential to understand what proportion of the total number of deaths in the population can be attributed to sepsis. This information is obviously critical for decisions about allocating investments in assistance, training and research. However, there is no good quality information on the proportion of deaths that are attributable to sepsis, not even from other countries. Our proposal is to estimate, among the cases of hospital deaths, what proportion is attributable to sepsis versus other groups of causes (cardiovascular diseases, cancer, etc. ).

Understanding attributable mortality from sepsis has several relevant operational and academic implications. From an operational point of view, the measurement of the attributable mortality fraction allows estimating the impact of future interventions aimed at reducing the occurrence of sepsis (handwashing campaign, actions by the Hospital Infection Commission, among others). From an academic point of view, this information will allow a better sample size calculation for future clinical trials in the area.

## Study objectives

*Primary:* To measure attributable mortality from nosocomial sepsis in hospitalized patients in Brazil.

*Secondary:*

1. Length of hospital stay in patients with or without sepsis
2. To assess mortality attributable to other hospitalization complications (infarction, stroke, pulmonary thromboembolism )
3. Evaluate the quality of completion of medical records
4. Assess the quality and consistency of filling in the hospital death certificate

## Methods

### Study design

Case-control study to be carried out through analysis of medical records.

### Sample size

The sample size calculation was performed using the Fleiss , Tytun and Ury method to estimate the power of a two-tailed test for proportion difference using the Hmisc package of the R software (version 3.5.0). The sample size was estimated for a power above 90% to detect an *odds ratio* of at least 1.4 assuming an incidence of nosocomial sepsis in controls of 15%. Two thousand seven hundred patients would be needed. We have chosen to round the number to 3,000 in order to ensure a safety margin.

## Eligibility criteria for institutions

This total of patients will be included in a group of 30 Brazilian hospitals that meet the following characteristics:

1. At least 100 active beds
2. Presence of intensive care unit and /ou emergency room
3. Availability to collect data for the study

## Eligibility criteria for patients

### Inclusion criteria

Each hospital will provide clinical, demographic and laboratory data for the last 50 deaths that occurred in the institution. Data from the patient who was discharged alive with a date and time closer to the date of death of the case will be used as controls. Fifty controls will be used per hospital, totaling 100 patients per hospital. Consecutive matching with the closest live high will ensure that any temporal impacts are minimized.

In addition to the general criteria mentioned, the specific inclusion criteria are:

- Patients over 18 years of age;
- Hospital stay for more than 24 hours;

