| Primary Purpose                   | To measure attributable mortality from nosocomial sepsis in hospitalized patients in Brazil.                                                                                                                                                                                                                                                                                                                           |
| secondary objectives              | 
 
1. Assess length of hospital stay in patients with or without sepsis
 
2. Assess mortality attributable to other hospitalization complications (infarction, stroke, pulmonary thromboembolism )
 
3. Evaluate the quality of completion of medical records
 
4. Assess the quality and consistency of filling in the hospital death certificate
 
 |
| Eligibility of cases and controls | Each hospital will provide clinical, demographic and laboratory data for the last 50 deaths that occurred in the institution. Data from the patient who was discharged alive with a date and time closer to the date of death of the case will be used as controls.                                                                                                                                                    |
| sample size                       | 30 hospitals, 100 patients in each hospital (50 cases and 50 controls), totaling 3,000 patients                                                                                                                                                                                                                                                                                                                        |

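### A quota of 50 deaths per hospital with no weight for death volume gives an equal-hospital average, which may differ from the share of hospital deaths the protocol sets out to estimate

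*Protocol*

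**What the plan says.** The Protocol document holds two protocol texts. This point refers to the second, which has separate eligibility sections and the inverse-probability-weighted analysis.

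- **Target.** Introduction: "Our proposal is to estimate, among the cases of hospital deaths, what proportion is attributable to sepsis versus other groups of causes". The same section explains why: "it is essential to understand what proportion of the total number of deaths in the population can be attributed to sepsis". The primary objective extends the aim to hospitalized patients in Brazil.
- **Sample.** Inclusion criteria: "Each hospital will provide clinical, demographic and laboratory data for the last 50 deaths that occurred in the institution", and "Fifty controls will be used per hospital, totaling 100 patients per hospital". The synopsis table gives the total: "30 hospitals, 100 patients in each hospital (50 cases and 50 controls), totaling 3,000 patients".
- **Hospitals.** Eligibility criteria for institutions sets a floor, "At least 100 active beds", with no ceiling and no size strata. One further criterion is "Availability to collect data for the study".
- **Time.** Inclusion criteria: "Consecutive matching with the closest live high will ensure that any temporal impacts are minimized". No calendar period is set for the 50 deaths. The two-year limit under Data collection reads as a limit on completing data entry.
- **Analysis.** The attributable fraction is Pc × (OR − 1)/OR by day, for each admission type, with Pc taken among the sampled non-survivors. The only weights described are for the probability of acquiring sepsis. Center enters as a random intercept.
- **Data items.** No count of deaths per hospital is listed.

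**The concern.** The target is a fraction of deaths, but the sample gives every hospital the same say. A 100-bed hospital and one many times larger each contribute 50 of the 1,500 deaths. If sepsis accounts for a different share of deaths in large hospitals than in small ones, the pooled Pc answers a different question from the one in the Introduction.

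Nothing in the analysis section restores volume. The sepsis weights address confounding. The random intercept cannot help, because every hospital is sampled at 50 deaths to 50 discharges, so the data carry no information on how many deaths it has.

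Time raises a related point. Pairing each death with the nearest live discharge balances cases and controls in time, which protects the odds ratio. Pc is computed among deaths only, so the pairing does not make it represent a year if the 50 deaths fall within a short window.

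The protocol offers the result for decisions on investment and for judging the effect of future prevention, so the meaning of the headline percentage matters.

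**Working it through.** **The plan's own figure.** OR 1.4 on 15% exposure in controls gives odds 1.4 × 0.15/0.85 = 0.2471, so 19.81% in cases. At two-sided alpha 0.05 (assumed; the protocol gives no alpha) and 90% power, the continuity-corrected size is 1,345 per group, or 2,690, against the stated 2,700. Power is 91.0% at 2,700 and 93.6% at 3,000. The sample size reproduces and this point does not touch it.

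**Weight per hospital.** 50/1,500 = 3.33% of sampled deaths, whatever the hospital's volume.

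**Equal-hospital against death-weighted fraction.** The documents give neither deaths per hospital nor sepsis share by size, so everything below is assumed. Take 15 small and 15 large hospitals. Death-weighted fraction = sum(deaths × fraction)/sum(deaths).

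- 200 and 800 deaths a year, fractions 10% and 20%: (200 × 10 + 800 × 20)/1,000 = 18.0%, against 15.0% under the quota.
- 150 and 1,000 deaths: (150 × 10 + 1,000 × 20)/1,150 = 18.7%, against 15.0%.
- 200 and 800 deaths, fractions 6% and 10%: (200 × 6 + 800 × 10)/1,000 = 9.2%, against 8.0%.

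**Through the protocol's formula.** Let R be the ratio of deaths in large to small hospitals, with one common OR. Equal-hospital Pc = (Pc small + Pc large)/2, which is 20.0% in every row. Weighted Pc = (Pc small + R × Pc large)/(1 + R). The fraction is Pc × 0.4/1.4 at OR 1.4 (the protocol's planning value) and Pc × 2/3 at OR 3 (assumed).

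| Pc small / large | R | Weighted Pc | Fraction at OR 1.4: equal / weighted | Fraction at OR 3: equal / weighted |
|---|---|---|---|---|
| 20% / 20% | 4 | 20.0% | 5.7% / 5.7% | 13.3% / 13.3% |
| 15% / 25% | 2 | 21.7% | 5.7% / 6.2% | 13.3% / 14.4% |
| 15% / 25% | 4 | 23.0% | 5.7% / 6.6% | 13.3% / 15.3% |
| 15% / 25% | 8 | 23.9% | 5.7% / 6.8% | 13.3% / 15.9% |
| 10% / 30% | 4 | 26.0% | 5.7% / 7.4% | 13.3% / 17.3% |
| 25% / 15% | 4 | 17.0% | 5.7% / 4.9% | 13.3% / 11.3% |

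Across these rows the difference runs from −2.0 to +4.0 percentage points. It is zero when Pc does not vary with size.

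**Precision cost of weighting.** Kish design effect = mean(w²)/mean(w)².

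- 200/800: 340,000/250,000 = 1.36, so 1,500/1.36 = about 1,103 effective deaths.
- 150/1,000: 511,250/330,625 = 1.55, so about 970 effective deaths.

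The interval for Pc widens by the square root, about 1.17 and 1.24 times.

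**Window.** 50/annual deaths × 52 weeks: 26 weeks at 100 deaths a year, 5.2 at 500, 2.6 at 1,000. The annual deaths are again assumed.

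**The case against.** **The stronger reading.** A reader might infer that the pooled figure simply is not the share of hospital deaths due to sepsis. The documents do not support that. The two figures differ only if the sepsis share or the OR varies with hospital volume, and the protocol is silent on both. Reversing the assumed gradient reverses the sign. This objection stands, so the point is conditional.

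**The window.** A reader might also take it as fact that the 50 deaths cover only a few weeks. No death counts or dates are given, and at 100 deaths a year they would span half a year. A local outbreak is diluted, since each hospital is 3.33% of cases. The schedule spreads center selection over two semesters and patient inclusion over six, so windows may be staggered across seasons. What remains is narrower: the sentence on temporal impacts covers the comparison of cases with controls, not Pc.

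**The statistical analysis plan.** Weighting is ordinary content for a plan that is not shown here. That is fair as to method, but the weights need a hospital death count that the protocol's data items do not include. The count could be obtained after chart collection, which lowers the urgency.

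**The quota is a sound design.** Equal numbers per center are common and efficient for a given number of charts. Weighting both deaths and discharges at R = 4 would cut power at OR 1.4 from 93.6% to about 85%, below the protocol's target of above 90%. This stands, and is why the OR model should carry no volume weight.

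**Brazil.** Volume weighting cannot turn 30 hospitals chosen by availability into a national sample. This stands too.

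**Conclusion.** The point holds in a conditional form. The equal weighting is certain from the text: 50 deaths per hospital, Pc from the pooled deaths, no volume weight and no count from which to build one. The pooled fraction is therefore close to an equal-hospital average, while the stated target is a proportion of deaths.

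Whether the two differ, by how much and in which direction cannot be determined from the documents. Under the assumed scenarios using the protocol's formula the gap runs from −2.0 to +4.0 percentage points, with zero if the sepsis share is unrelated to hospital size. Those scenarios assume two equal groups of hospitals and a common OR.

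The quota itself is not the defect; what is missing is the link from the quota to the target. As planned, the sponsor could not show whether its headline percentage is a share of deaths, even within the participating hospitals. This is a cheap improvement to make, not a flaw that invalidates the design.

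**What to change.** 1. Add two hospital-level data items: the number of eligible deaths (same age and length-of-stay criteria) over one common 12-month period, and the first and last calendar dates of the 50 sampled deaths.
2. Leave the odds-ratio model and its test as planned, with no volume weight.
3. Report the attributable fraction twice: with Pc as planned, and with Pc weighted by hospital death volume. Each sampled death from hospital h gets weight D_h/50, where D_h is that hospital's 12-month count, applied within each day and admission type. The interval should reflect the weights.
4. Report the windows, and confine the sentence on temporal impacts to the case-control comparison.
5. State that either figure describes the 30 participating hospitals, which were chosen by availability, and is not a probability-based estimate for Brazil.

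**Cost.** One administrative count and two dates per hospital, with no extra charts. The weighted figure has a wider interval: a design effect of about 1.36 to 1.55 under the assumed volumes, and more if a few very large hospitals dominate. Weighting Pc alone leaves any variation of the OR with hospital size uncorrected, and this should be said beside the result.

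Spreading the 50 deaths over a full year would trade a simple consecutive rule for register sampling and older charts. It is not needed to resolve this point.

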## Exclusion criteria

Discharge cases due to transfer, evasion or home care should be excluded..

## Data collection

Data collection will be performed by each hospital using an electronic data collection system designed specifically for the study. The filling will be done by each center based on data from medical records, according to local availability, respecting the maximum period of completion of two years. All data collected will be anonymous, in order to preserve the identity of the participants and guarantee confidentiality. The data to be collected are:

1. Charlson Comorbidity Index )
2. Reason for admission: Scheduled versus unscheduled. Presence of infection as the cause of hospital admission (defined as admission with a primary diagnosis of infectious pathology by ICD 10).
3. Physiological variables: Blood pressure, heart rate, respiratory rate, level of consciousness.
4. Laboratory variables: Renal function (serum creatinine), blood count, C-reactive protein (if available), coagulogram , bilirubin, serum lactate .
5. Result of all cultures (blood, tracheal secretion, urine or other sites) collected during hospitalization.
6. Length of stay in hospital
7. Use of intra-hospital resources

- a. Number of imaging tests performed to elucidate an infectious focus
- b. Need for surgical procedures
- c. Intensive care stay
- d. Use of supportive therapy such as mechanical ventilation, renal replacement therapy, use of vasopressors.

Laboratory and physiological variables will be collected from admission and during the first three days of the patient's hospitalization. In the event of addition, initiation or change of antimicrobial regimen and/or collection of some type of microbiological examination (culture), we will perform physiological and laboratory data collection again for an additional period of three days before and after the date of your occurrence. in order to monitor the occurrence of organic dysfunction associated with a suspected infectious condition (sepsis). In these situations, we will also note:

1. The causative focus of sepsis
2. The antibiotic prescribed and its suitability (i.e., whether the antibiotic prescribed at the initial time was effective against the pathogen that eventually proved to be the cause of the event )
3. Whether or not the infection was associated with a surgical procedure or invasive device (prosthesis infection, catheter-related bloodstream infection, etc. ).

We will also note the occurrence of other clinical complications, such as:

1. Pulmonary thromboembolism
2. Myocardial ischemia/myocardial infarction
3. Stroke (ischemic or hemorrhagic)

For cases (that is, for hospital deaths), we will collect the information contained in the death certificate (immediate cause and its sequence, as well as contributing causes).

*Definition of the exposure factor:* The exposure of interest is nosocomial sepsis, that is, a nosocomial infection that courses with the occurrence of organic dysfunction. As organic dysfunction, we will consider the presence of at least one of the factors below when starting or changing the therapeutic antimicrobial regimen in a hospitalized patient:

1. Systolic pressure < 90 mmHg or mean pressure < 65 mmHg or pressure drop > 40 mmHg
2. PaO2 /FiO2 ratio <300 or O2 requirement to maintain SpO2 > 90
3. Lowering the level of consciousness
4. Creatinine > 2.0 mg /dL or urine output less than 0.5mL/Kg/h in the last 2 hours
5. Bilirubin > 2mg/dL
6. Platelet count < 100,000mm^3

7. Lactate above the reference value
8. Coagulopathy (INR > 1.5 or APTT > 60 sec )

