## **Statistical analysis**

Traditional univariate analysis comparing groups (case and control) with respect to the variables described above will be performed using t-test or Mann-Whitney test for continuous variables (as appropriate depending on the occurrence of normality) and Chi-square test for comparison of proportions.

The following approach will be used to calculate attributable fraction calculation for each admission type: The inverted probability weights (IPW) for each patient will be calculated, representing the cumulative risk of the patient acquiring sepsis during hospitalization, under a multivariable logistic regression analysis including baseline age, Charlson Comorbidity Index, and a time-dependent variable for the occurrence of clinically relevant events. We will estimate the association between sepsis occurrence on hospital mortality within 28 days through a mixed logistic regression model weighted by IPW. The model will include the participant center as a random intercept, and age, Charlson Comorbidity Index, infection at admission, IPW, and the accumulated dependent time variables of sepsis occurrence and clinically relevant events with their interaction with time (modeled with a third-degree polynomial). From the daily odds ratios

estimated by the model, the Miettinen formula will be used to calculate the attributable mortality of sepsis:

$$P_{c_i} * \frac{OR_i - 1}{OR_i}$$

*i = day,  $P_c$  = proportion of patients that had sepsis among non – survivors*

We will also present the marginal effect of having one sepsis episode on the whole period, with an estimate of average attributable fraction obtained from the model. All analyses will be performed using the R software

*Sensitivity analysis:* Different definitions of sepsis will be explored; the same analysis method described above will be used for different definitions as sensitivity analyses. An internal consensus was created within the steering committee on probability degrees of sepsis according to combinations of use of antibiotics, organ failure, results of cultures, and occurrence of clinically relevant events. Two sensitivity analyses will be made, one estimating the attributable fraction considering definitive, very probable, and probable sepsis, and a second sensitivity analysis considering only definitive and very probable sepsis.

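### No admission diagnosis beyond scheduled/unscheduled and infection yes/no is listed for collection or modelled, so the sepsis odds ratio and attributable fraction are likely to carry residual confounding, probably upward

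*Protocol*

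**What the plan says.** The protocol file holds two texts. References here are to the later one, which has separate eligibility sections and the weighted analysis.

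- **Control selection (Inclusion criteria).** The control is "the patient who was discharged alive with a date and time closer to the date of death of the case". The stated reason for the pairing is that it "will ensure that any temporal impacts are minimized".
- **Restrictions (Inclusion and Exclusion criteria).** "Patients over 18 years of age"; "Hospital stay for more than 24 hours"; and "Discharge cases due to transfer, evasion or home care should be excluded". None concerns diagnosis or hospital service.
- **Reason for admission (Data collection, item 2).** Scheduled versus unscheduled, and presence of infection as the cause of admission, "defined as admission with a primary diagnosis of infectious pathology by ICD 10". No other admission diagnosis is listed.
- **Weight model (Statistical analysis).** Age, Charlson index and a time-dependent term for clinically relevant events.
- **Outcome model (Statistical analysis).** A random intercept for center, then "age, Charlson Comorbidity Index, infection at admission, IPW", and the time-dependent sepsis and event terms with their interaction with time. The attributable fraction is calculated separately by admission type with the Miettinen formula.
- **Cause information (Data collection).** Taken from the death certificate, for deaths only.

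**The concern.** Deaths come disproportionately from high-risk admission diagnoses, while the nearest live discharge is drawn from the whole adult hospital population. If the acute reason for admission affects both the chance of nosocomial sepsis and the chance of dying, and the adjustment does not carry it, part of the case-control difference in sepsis frequency reflects diagnosis and is counted as an effect of sepsis.

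The primary result is a fraction built directly on the odds ratio. The Introduction wants it for investment decisions, for judging prevention programmes and for sizing later trials. It also wants sepsis set against groups such as cardiovascular disease and cancer. A diagnosis group that is never abstracted from the 3,000 records cannot be added at the analysis stage.

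**Working it through.** **1. The plan's own figures.** Sample size: 15% sepsis in controls, odds ratio 1.4, two-tailed, power above 90%. Alpha is not stated; 0.05 is assumed.

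- Sepsis odds in cases = 1.4 × 0.15/0.85 = 0.2471, so the proportion is 0.2471/1.2471 = 19.8%.
- The usual two-proportion formula gives 1,304 per group. With the continuity correction, n/4 × [1 + √(1 + 4/(n·d))]² with d = 0.0481, it gives 1,345 per group, or 2,690 in total. The stated 2,700 reproduces, and the sample size is not in dispute.
- Miettinen fraction at these values: 0.198 × (1.4 − 1)/1.4 = 5.7%.

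**2. What the planned terms can carry.**

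- *Admission type* separates elective from emergency, but trauma, acute stroke and an emergency laparotomy can all be unscheduled.
- *Infection at admission* separates infectious from non-infectious reasons, but not one non-infectious reason from another. It is also absent from the weight model.
- *Charlson index* describes comorbidity. It partly carries cancer and cerebrovascular disease, but not trauma or an acute abdomen.
- *Clinically relevant events* are not defined further. The complications listed under Data collection are thromboembolism, myocardial ischemia or infarction, and stroke. Whether a stroke present at admission counts is not stated.
- *Weighting* removes only confounding by the terms in the weight model.

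**3. How large the remainder could be.** The documents give no figure for this, so everything about the omitted group is assumed. Let U be a high-risk diagnosis group within a stratum of equal measured covariates. Assumptions: U covers 30% or 50% of admissions; death risk is 4% without U and without sepsis; the sepsis risk without U is set so that 15% of controls are septic. Taking all deaths and a random share of live discharges leaves the odds ratio unchanged, so population cells suffice.

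Worked case: U 30%, odds ratio 3 with sepsis and 3 with death, true sepsis odds ratio 1.0.

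- Without U: sepsis 10.57%, death 4%. With U (odds × 3): sepsis 26.17%, death 11.11%.
- Dead and septic: 0.7 × 0.1057 × 0.04 + 0.3 × 0.2617 × 0.1111 = 0.01168. Dead, not septic: 0.04965.
- Alive and septic: 0.14080. Alive, not septic: 0.79787.
- Apparent odds ratio = (0.01168 × 0.79787)/(0.14080 × 0.04965) = 1.33.
- Sepsis among deaths = 0.01168/(0.01168 + 0.04965) = 19.0%. Fraction = 0.190 × 0.333/1.333 = 4.8%, where the truth is 0.

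All cases, as U 30% / U 50%:

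| OR of U with sepsis, death | True 1.0 appears as | True 1.4 appears as | Fraction at OR 1.4 | Fraction at apparent OR |
|---|---|---|---|---|
| 1.5, 1.5 | 1.04 / 1.04 | 1.45 / 1.46 | 5.8% / 5.8% | 6.4% / 6.4% |
| 2, 2 | 1.12 / 1.12 | 1.57 / 1.56 | 6.2% / 6.2% | 7.8% / 7.7% |
| 3, 3 | 1.33 / 1.28 | 1.85 / 1.78 | 7.0% / 6.8% | 11.4% / 10.5% |
| 5, 5 | 1.78 / 1.56 | 2.46 / 2.17 | 8.6% / 7.9% | 17.9% / 14.9% |
| 2, 0.5 | 0.91 / 0.89 | 1.27 / 1.24 | 5.2% / 5.1% | 3.9% / 3.5% |

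In this set-up, adjusting for U returns the true odds ratio. The calculation does not model the daily time structure, the center intercept or the weighting. It shows how strong the leftover effect of diagnosis would have to be, not what the planned model will return.

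**The case against.** Much can be said for the plan, and several stronger readings should be resisted.

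- *A reader might infer that the reason for admission is reduced to infection yes/no.* It is not. The same item records scheduled or unscheduled, and the fraction is estimated by admission type.
- *A reader might infer that the control sampling is itself faulty.* The target is hospitalized patients in Brazil, and live discharges from the same hospital suit it. The gap is in the covariates.
- *A reader might point to childbirth as the main driver.* The eligibility criteria do admit deliveries, but the documents do not say under which admission type they fall. A simulation with assumed inputs (20-30% obstetric, sepsis 0.5%, almost no deaths) moved a true 1.4 only to about 1.42-1.49 once age was adjusted.
- *A reader might conclude that the odds ratio is shown to be inflated.* It is not. Upward bias needs diagnosis to act in the same direction on sepsis and death. The last row of the table reverses the sign, and the first row is negligible.

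Two further objections stand in part. Item 2 does not say that the ICD-10 code is discarded; if it is kept, only the model term is missing. Admission physiology and laboratory values, surgery and intensive care stay are also collected and could serve as partial proxies. But they are not named in either model, and surgery or intensive care may follow sepsis rather than precede it. Nor can the matter simply be left to a separate analysis plan, since the protocol already lists both the data items and the model terms.

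**Conclusion.** The point holds as a likely source of residual confounding, probably upward, of unknown size. What the text supports is that controls are unrestricted on diagnosis, that no admission diagnosis is listed beyond scheduled/unscheduled and infection yes/no, and that neither model has a diagnosis term.

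The direction rests on the judgement that acute non-infectious diagnoses raise both sepsis and death at equal measured covariates. The size rests wholly on assumed inputs: negligible at odds ratios of 1.5 on both, but at 3 on both enough to produce a spurious fraction of 4.0-4.8% from a null effect, close to the 5.7% implied at the design values. That makes a cheap correction worthwhile. It does not show that the planned estimate will be wrong by any given amount.

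**What to change.** 1. In Data collection, item 2, store the primary ICD-10 code, or a coarse diagnosis group derived from it, for cases and controls alike. The primary diagnosis must already be read to fill the infection field.
2. Add that group as a baseline term in both the weight model and the outcome model.
3. Keep the grouping coarse and merge sparse low-risk categories, such as obstetric, into an other/low-risk level. If 5-15% of 1,500 controls were obstetric (75-225) with 0.5% sepsis (both assumed), only 0.4-1.1 would be septic, and an unstabilised weight could reach 1/0.005 = 200.
4. Stabilise or truncate the weights. A separate run without obstetric patients is not needed.

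Cost: one stored field, a few more model parameters and, with coarse groups, slightly wider intervals. If collection is already closed and the code was not kept, the gap should be reported as a limitation of the attributable fraction.

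### Secondary objective 2 concerns complications of hospitalization, but the protocol lists no item that separates an in-hospital infarction, stroke or embolism from one that caused the admission

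*Protocol*

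**What the plan says.** The file holds two versions of the protocol. I cite the second, which has the patient eligibility criteria and the weighted analysis; the data list in the first has the same gap.

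- **Objective.** Secondary objective 2 (Study objectives, repeated in the synopsis) is "To assess mortality attributable to other hospitalization complications (infarction, stroke, pulmonary thromboembolism").
- **Events.** Data collection introduces them with "We will also note the occurrence of other clinical complications, such as" and then names pulmonary thromboembolism, "Myocardial ischemia/myocardial infarction" and stroke. None of the three carries a definition, an onset date or a mark for presence on arrival.
- **Admission.** Item 2 of the same list is "Reason for admission: Scheduled versus unscheduled. Presence of infection as the cause of hospital admission", the latter taken from the primary ICD-10 diagnosis.
- **Eligibility.** Patients must be adults with "Hospital stay for more than 24 hours". The only exclusions are discharges through transfer, evasion or home care.
- **Analysis.** The model for the sepsis weights includes "a time-dependent variable for the occurrence of clinically relevant events". Such events also enter the outcome model and the graded sepsis definitions of the sensitivity analyses. The term is not defined.

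**The concern.** An attributable fraction for complications of hospitalization has a clear target: deaths that would not have happened had the event not arisen during the stay. A stroke that brought the patient to hospital is outside that target. It is part of the baseline risk.

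The protocol applies this distinction to infection. It records infection as the cause of admission, limits the exposure to nosocomial sepsis, and adjusts for infection at admission. For the three comparator events it asks only whether they occurred. A chart abstractor with a patient admitted for stroke has no listed field in which to say so, and may tick stroke as having occurred. Thirty hospitals abstract their own charts, so sites may also differ in how they read the item.

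Two things are at stake. The fractions under objective 2 may mix two kinds of event, and would then not be comparable with the nosocomial-sepsis fraction. And if the clinically relevant events of the Statistical analysis section include these three, the same ambiguity reaches the sepsis weights and the outcome model.

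An analysis plan cannot repair this by itself, because onset that was never abstracted from the chart is not available at analysis.

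**Working it through.** **Step 1. The items side by side.**

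| | Infection / sepsis | Infarction, stroke, embolism |
|---|---|---|
| Target | nosocomial sepsis | hospitalization complications |
| Cause of admission recorded | yes: "Presence of infection as the cause of hospital admission (defined as admission with a primary diagnosis of infectious pathology by ICD 10") | no item listed |
| Timing recorded | data for three days before and after each antimicrobial change or culture | none listed |
| Baseline adjustment | infection at admission | none stated |
| Audit and adjudication (Data management) | sepsis, in all cases | none stated |

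The other admission item, "Reason for admission: Scheduled versus unscheduled", does not separate them: an unscheduled admission may be for a stroke or for something else. The death certificate gives a causal sequence, but for cases only, so it cannot classify events in controls.

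**Step 2. Can admission events enter?** Yes. Neither the inclusion nor the exclusion criteria remove patients admitted for these conditions.

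**Step 3. Size, if they do.** The protocol gives no rate, odds ratio or attributable fraction for these events, so there is no figure of its own to reproduce. It names no estimator for objective 2, so I assume the Miettinen form it states for sepsis:

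AF = Pc × (OR − 1)/OR, with Pc the proportion of deaths with the event.

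Let f be the share of counted events among the deaths that was present on admission, and let the OR be the same for both types.

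- All events counted: AF_all = Pc × (OR − 1)/OR
- In-hospital events only: AF_in = Pc × (1 − f) × (OR − 1)/OR
- Ratio: AF_all / AF_in = 1/(1 − f)

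The ratio does not depend on Pc or OR. To give a scale, with Pc = 10% (assumed) and a range of assumed OR:

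| Assumed f | 1/(1 − f) | AF_in, OR 1.4 | AF_in, OR 2 | AF_in, OR 3 |
|---|---|---|---|---|
| 0 (= AF_all) | 1.00 | 2.86% | 5.00% | 6.67% |
| 25% | 1.33 | 2.14% | 3.75% | 5.00% |
| 50% | 2.00 | 1.43% | 2.50% | 3.33% |
| 75% | 4.00 | 0.71% | 1.25% | 1.67% |

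Example: OR 2, f = 50%: 0.10 × 0.50 × (2 − 1)/2 = 2.5%, against 0.10 × (2 − 1)/2 = 5.0% with all events counted.

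**Step 4. Does the analysis text supply the missing timing?** Only in part. A time-dependent variable needs a day of occurrence, so some events must be dated. But the text does not say that they are these three, and no rule covers an event already present at admission.

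**The case against.** The best answer is that the protocol's own words exclude admission events. It speaks of hospitalization complications, and an admitting diagnosis is not a complication of that admission. The list in Data collection is a summary of domains for a purpose-built electronic form that we do not see. That form may well hold dates, and centers receive training and monitoring. This stands in part. The word shows the intent, so it cannot be said that admission events *will* be counted. It is not an instruction to the abstractor, however, and the section states the principle explicitly for infection and not for these events.

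A second objection concerns the time-dependent variable. If the clinically relevant events are these three, they are dated, and events on the day of admission can be found at least approximately. If they are not, nothing carries over to the sepsis model. This also stands as a limit: one cannot claim both that separation is impossible and that the primary model is affected. What remains is that the link is not stated and that no rule covers events present on admission.

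A reader might infer more: that objective 2 would mostly measure admissions for stroke and infarction, or that its fractions would be several times too high. The documents do not support this. They give no prevalence, no odds ratio and no share present on admission. Any multiplier restates the share that one assumes, and also takes for granted that every admitting event is recorded as a complication. Nor can one lean on emergency departments: the hospital criteria ask for an intensive care unit and/or an emergency room, so the latter is not clearly required.

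**Conclusion.** The point holds as a gap in what is collected for a named secondary objective. The protocol targets in-hospital events, lists only their occurrence, keeps patients admitted for the same conditions, and has an admission-cause item for infection alone. Events that caused the admission may therefore enter the fraction for hospitalization complications.

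The size is 1/(1 − f) under two assumptions: the Miettinen form applies, and the odds ratio is the same for both onset types. Since f is unknown, this shows sensitivity and does not estimate the bias. Even an assumed f of 25% overstates the fraction by a third.

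The effect on the primary sepsis analysis is conditional. It arises only if the clinically relevant events include these three and no rule deals with those present at admission. A reader should not take this point as showing that the primary result is biased.

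The change should be made: it is small, and without it the meaning of objective 2 depends on how each site reads the item.

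**What to change.** In Data collection, for each of the three events and for cases and controls alike, record:

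1. the onset date;
2. whether the event was the reason for admission, from the primary ICD-10 diagnosis as is already done for infection.

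Then state that, for objective 2, only events with onset after admission count as hospitalization complications, and that events present on admission enter as a baseline covariate. In Statistical analysis, define the clinically relevant events and say whether they are these events with post-admission onset.

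The cost is two extra fields per event, read from a chart that is already open, and a few sentences of protocol text. If abstraction has started at a site, completed charts with one of these events would need a second look. Fewer events will count, possibly many fewer if f is large, so the estimates for objective 2 will be less precise.
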